## Assignment of interventions: Blinding

### Who will be blinded {17a}

Given the nature of intervention, it is challenging to blind participants and staff to group allocation. However, allocation status of participants is kept hidden from those evaluating the outcomes. To minimize potential bias, all outcomes not based on self-reporting will be assessed by an evaluator who is unaware of the participants’ treatment allocation.

### Procedure for unblinding if needed {17b}

N/A: Only outcome evaluators are blinded in this study. So unblinding does not apply to this study’s design.

## Data collection and management

### Plans for assessment and collection of outcomes {18a}

Outcome assessments will be meticulously documented by the research evaluator on the case report form (CRF), identifying participants by their study ID numbers and initials, thus ensuring confidentiality. Baseline assessments will be conducted prior to surgery. Evaluations for postoperative urinary tract infection are scheduled at 3 days, 1 week, 2 weeks, 3 weeks, and 4 weeks post-surgery. Assessments for bladder dysfunction post-operation will occur at 1 week, 2 weeks, 3 weeks, 1 month, and 3 months post-surgery. Urodynamic results will be collected 1 month post-surgery. Follow-up will be conducted through WeChat APP or telephone.

### Plans to promote participant retention and complete follow-up {18b}

To enhance participant retention and ensure comprehensive follow-up, individuals will be informed about the study’s design, its significance, and the potential benefits of participation during the recruitment phase. Each participant has an assigned a research member responsible for data collection and management. Participants will be informed of their right to alter intervention options or withdraw from the study. And all the information and results of these participants will be collected with permission.

### Data management {19}

All collected data will be securely stored with backups created, and access to the data will be restricted. Once all participants have completed their follow-up and the data is verified, the primary investigator will lock the raw data to prevent further changes. All study-related materials will be retained by the Research Office of the First Affiliated Hospital of Army Medical University. Data will be available to professional statisticians for statistical analysis while maintaining the integrity of the raw data files for future reference.

### Confidentiality {27}

Participants’ privacy and confidentiality will be rigorously protected. All personal data will be stored securely with limited access. The identification details of participants will not be utilized in any aspect of the research dissemination.

### Plans for collection, laboratory evaluation, and storage of biological specimens for genetic or molecular analysis in this trial/future use {33}

N/A: This study does not involve the collection, evaluation, or storage of biological specimens for genetic or molecular analysis.

## Statistical methods

### Statistical methods for primary and secondary outcomes {20a}

An intention-to-treat analysis will be performed, utilizing the last available measurement for instance of data lost. The collected data was analyzed using SPSS 20.0 software. Continuity data will undergo normality testing; those with a normal distribution will be analyzed using an independent sample *t* test, while those with a skewed distribution will be assessed using non-parametric test. Chi-square test was used for enumeration data, mean value ± standard deviation ( $$\overline{x }$$±S) for measurement data. When *p* < 0.05, the difference can be considered statistically significant.

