#### Exit criteria

→Participants are reluctant to continue the study.→If researchers believe that continued participation would be detrimental to patient treatment.

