## Interventions

### Explanation for the choice of comparators {6b}

In the control group, catheters will be removed seven days post-operation as determined by the attending physician. If residual urine volume (RUV) exceeds 100 mL upon catheter removal, this will indicate urinary retention, promoting reinsertion of the catheter. The catheter will be removed on a weekly basis thereafter, until RUV is less than 100 mL [22–24].

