### Outcomes {12}

#### Primary outcomes

The primary outcome measure for this study is the rate of bladder function recovery (Bladder Function Recovery Grade II or higher) 2 weeks post-surgery. Bladder function recovery is quantified by a RUV less than 100 mL following spontaneous urination after catheter removal. The grading system for bladder function recovery is as follows [27]: Grade I: Patient has a bladder fullness sensation and urination desire, can urinate spontaneously upon catheter removal, and has a RUV of less than 50 mL, indicating effective bladder function recovery; Grade II: Patient has a bladder fullness sensation and the desire to urination, can urinate spontaneously upon catheter removal, but the RUV is between 50 and 100 mL, suggesting slightly diminished bladder function recovery. Grade III: Patient lacks bladder fullness sensation or urination desire, can urinate spontaneously upon catheter removal, but RUV exceeds 100 mL, reflecting poor bladder function recovery; Grade IV: Patient has no sensation of spontaneous urination and cannot urinate independently with various interventions after catheter removal, indicating lack of bladder function recovery.

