### Methods in analysis to handle protocol non-adherence and any statistical methods to handle missing data {20c}

The intention-to-treat analysis will be used in this study. Missing objective data will be interpolated with mean values, and the missing subjective data will not be interpolated. The effectiveness of these methods for handling missing data will be assessed through sensitivity analysis. Further, to evaluate the impact of non-adherence on study outcomes, the per-protocol analysis will also be adopted.

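### The protocol gives two incompatible missing-data rules, names neither as primary, and leaves the handling of the binary week-2 endpoint undetermined; mean substitution does not suit that endpoint

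*Protocol article*

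**What the plan says.** The protocol article treats missing data in two places.

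- Statistical methods {20a}: "An intention-to-treat analysis will be performed, utilizing the last available measurement for instance of data lost". No data type is excepted.
- Non-adherence and missing data {20c}: "Missing objective data will be interpolated with mean values, and the missing subjective data will not be interpolated". The next sentence adds: "The effectiveness of these methods for handling missing data will be assessed through sensitivity analysis". A per-protocol analysis is also planned there.

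Under the Primary outcomes heading, the endpoint concerned is defined as follows: "The primary outcome measure for this study is the rate of bladder function recovery (Bladder Function Recovery Grade II or higher) 2 weeks post-surgery". It has an objective part, "Bladder function recovery is quantified by a RUV less than 100 mL following spontaneous urination after catheter removal", and the grades also carry a subjective part. Grade I, for instance, begins: "Patient has a bladder fullness sensation and urination desire".

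Three further passages bear on which values could be missing or carried forward. In the intervention arm the catheter comes out on postoperative day 3 and RUV is measured from then (Intervention description {11a}). In the control arm it comes out on day 7, and if it has to be reinserted, "The catheter will be removed on a weekly basis thereafter, until RUV is less than 100 mL" (section {6b}). The Exit criteria include researcher judgement: "If researchers believe that continued participation would be detrimental to patient treatment".

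**The concern.** Both rules are current text, and they conflict for both kinds of data. Objective data get either the last value or a mean. Subjective data get either the last value or nothing. Because the week-2 grade draws on both kinds, an analyst cannot tell from the protocol what to do with a patient whose week-2 grade is missing. Participants and staff are not blinded, so a rule left open can be chosen after results by arm are known.

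Mean substitution has a fault of its own. Recovered or not recovered has no mean category. If mean RUV is substituted and then compared with 100 mL, the outcome of every patient given that mean is decided as a block. For continuous outcomes such as the urodynamic measures, substituting the arm mean adds patients but no variability, so the standard error is too small.

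At stake are the size of the primary treatment difference and the validity of the tests on continuous outcomes.

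**Working it through.** **Inputs from the protocol (Sample size {14}).** Planning recovery rates p1 = 0.7895 (intermittent catheterization, IC) and p2 = 0.3889 (control), a true difference of 0.4006; 39 patients per arm; 10–15% expected loss. The protocol states no figure for the effect of its missing-data rules, so there is none to reproduce.

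**Assumptions (not in the protocol).** (a) A fraction m = 10–15% is missing at week 2 in each arm, about 4–6 of 39. The protocol's 10–15% also covers refusal to participate, so this is an assumption. (b) Missing patients have the same true recovery rates as those observed. (c) RUV is lognormal with log-SD s = 0.8 to 1.2. (d) The mean is imputed for RUV and then cut at 100 mL.

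**1. Imputed RUV.** Setting P(RUV < 100) = p gives mean = exp(ln 100 − s·z(p) + s²/2), with z(0.7895) = 0.805 and z(0.3889) = −0.282.

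| s | IC arm mean | Control arm mean | Overall mean |
|---|---|---|---|
| 0.8 | 72 mL | 173 mL | 122 mL |
| 1.0 | 74 mL | 219 mL | 146 mL |
| 1.2 | 78 mL | 288 mL | 183 mL |

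With arm means, every missing IC patient counts as recovered and every missing control patient as not recovered. With the overall mean, every missing patient in both arms counts as not recovered. Section {20c} does not say which mean is meant.

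**2. Effect on the primary difference.**

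- Arm means: [(1 − m)p1 + m] − (1 − m)p2. At m = 0.10: 0.8106 − 0.3500 = 0.461. At m = 0.15: 0.8211 − 0.3306 = 0.491.
- Overall mean: (1 − m)(p1 − p2). At m = 0.10: 0.361. At m = 0.15: 0.341.

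At 15% missing, the same data can therefore give about 34 or 49 points, depending on the mean chosen.

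**3. Continuous outcomes.** Simulation with 39 per arm, normal data and no true difference, two-sided 5% t test:

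| Missing per arm | Arm mean | Overall mean | Observed cases only |
|---|---|---|---|
| 4 | 7.8% | 4.9% | 4.9% |
| 6 | 9.7% | 5.0% | 4.9% |

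The cause in the arm-mean column is the standard error. With o observed of n = 39, its ratio to the correct one is √[o(o − 1)/(n(n − 1))], which is 0.90 for o = 35 and 0.84 for o = 33. The overall mean keeps the type I error near 5% but shrinks a true difference by the factor 1 − m, to 90% or 85% of its size.

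**4. Last value carried forward.** Let q1 and q2 be the week-1 recovery rates that would be carried (assumed 40–60% in IC and 0–20% in control; not in the protocol). The difference is [(1 − m1)p1 + m1q1] − [(1 − m2)p2 + m2q2].

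| q1, q2 | m = 10% both | m = 15% both | 15% IC, 5% control | 5% IC, 15% control |
|---|---|---|---|---|
| 0.5, 0.1 | 40.1 | 40.1 | 37.2 | 42.9 |
| 0.4, 0.2 | 38.1 | 37.1 | 35.2 | 40.9 |
| 0.6, 0.0 | 42.1 | 43.1 | 39.2 | 44.9 |

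Against a true 40.1 points, the result lies on either side and can be almost unchanged. With the same carried rate in both arms (30%) and no true difference, the simulated type I error was 4.8–5.2%.

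**The case against.** Several points for the plan carry weight.

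- Section {20c} promises a sensitivity analysis of the missing-data methods. That softens the problem, but it does not say which method is primary and which is the check.
- A reader might infer that carrying the last value forward favours IC, because IC patients are measured from day 3 and control patients only from day 7. The documents do not support a direction. All participants have scheduled assessments at weeks 1 and 2. A control patient with RUV below 100 mL at day 7 would be carried as a success, and an IC patient lost on day 4 would be carried at an early value. What stands is that the measurement histories differ by arm and that a control patient lost before day 7 has no post-removal value to carry.
- A reader might also infer that either rule understates standard errors and inflates the type I error. This is shown only for arm-mean substitution, and the protocol does not say that arm means are intended.
- Because missing subjective data are not to be imputed, the grade may not be mean-imputed at all. That is fair, and it shows that the rule is undetermined.
- Patients taken out on researcher judgement may be those doing badly, but this is conjecture. The Discussion says that all subjects count in the primary outcome regardless of compliance.
- Under the assumptions used here, the overall-mean reading classifies missing patients exactly as counting them as not recovered would. It does so only by accident of the RUV distribution, which is no reason to keep it.

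**Conclusion.** The conflict between sections {20a} and {20c} is real and reaches the primary endpoint. It is not detail left to an analysis plan, because the protocol states both rules. Mean substitution is unsuitable for the yes/no outcome under either reading: a true 40-point difference becomes 46–49 points with arm means or 34–36 with an overall mean. These figures rest on lognormal RUV, the planning rates, 10–15% missing at week 2 and imputation before the cut at 100 mL. The inflated type I error of about 8–10% applies to continuous outcomes under arm-mean substitution only; the overall mean leaves it near 5% but dilutes the difference. For last value carried forward, the supported conclusion is possible bias in either direction (37–43 points with equal loss, 35–45 with unequal loss, under the assumed week-1 rates). Neither a fixed advantage for IC nor a general understatement of standard errors is shown.

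**What to change.** Reconcile the two sections and delete mean substitution.

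- **Primary outcome.** State one rule for the week-2 grade as a whole, covering its objective and subjective parts. For example, analyse all randomised patients and count missing week-2 status as not recovered in both arms. Multiple imputation as the primary rule would also be defensible; what matters is that one rule is named before the data are seen.
- **Sensitivity analyses.** Name multiple imputation by arm, using the available RUV and grade assessments, and a tipping-point analysis. They are needed because counting missing as not recovered is not always conservative. With 5% missing in IC and 15% in control, the difference is 0.7895 × 0.95 − 0.3889 × 0.85 = 0.420, above the true 0.401.
- **Continuous outcomes.** Use a mixed model or multiple imputation where measures are repeated, and observed data or multiple imputation otherwise.

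The cost is a change of wording and a little more analysis. Recovery rates fall somewhat in both arms: with equal loss of 10–15%, to 71–67% in IC and 35–33% in control, a difference of 36–34 points. The planned sample size figure is not affected by the rewording.

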## Abstract

**Background:**

Bladder dysfunction, notably urinary retention, emerges as a significant complication for cervical cancer patients following radical hysterectomy, predominantly due to nerve damage, severely impacting their postoperative quality of life. The challenges to recovery include insufficient pelvic floor muscle training and the negative effects of prolonged postoperative indwelling urinary catheters. Intermittent catheterization represents the gold standard for neurogenic bladder management, facilitating bladder training, which is an important behavioral therapy aiming to enhance bladder function through the training of the external urethral sphincter and promoting the recovery of the micturition reflex. Nevertheless, gaps remain in current research regarding optimal timing for intermittent catheterization and the evaluation of subjective symptoms of bladder dysfunction.

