### Eligibility criteria {10}

#### Inclusion criteria

→Prospective enrolment of patients diagnosed with cervical cancer stages IA1 (infiltration of lymphatic vasculature space), IA2, IB1, IB2, and IIA1, according to the FIGO 2018 classification [21].→Patients underwent Laparoscopic RH and pelvic lymphadenectomy.→Aged 20 to 65 years, and BMI < 30 kg/m^2^.→Classified as I or II under the American Society of Anesthesiologists (ASA) classification.→A score of more than 75 points on the preoperative Barthel self-care ability assessment.

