### Sample size {14}

Based on the bladder function recovery rate at 2 weeks post-surgery (Bladder Function Recovery Grade II or higher) observed in pretest, the sample size was determined. The recovery rate for the IC group was 78.95%, compared to 38.89% IDUCs group. Using a unilateral *α* of 0.025, a desired power of 0.9 (i.e., 1 − *β* = 0.9) and the margin of 5%, the sample size was calculated using the following formula.$$n=\frac{{2\overline{p }\overline{q }\left({z}_{\alpha }+{z}_{\beta }\right)}^{2}}{{\left({p}_{1}-{p}_{2}\right)}^{2}}$$

Based on these parameters, the calculated sample size for each group was determined to be 35 cases. To facilitate 1:1 randomization, a total of 70 cases would be required. However, anticipating potential loss due to follow-up dropouts and refusal of participation (estimated at 10–15%), the final minimum number of research subjects for each group was determined to be 39 cases. Therefore, at least 78 participants are deemed necessary to ensure sufficient statistical power for this study.

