### Methods for additional analyses (e.g., subgroup analyses) {20b}

N/A: The primary analysis is sufficient to address the research question. No additional analyses were required.

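### The primary comparison is an unadjusted chi-square although age and FIGO stage are known before allocation; prespecified adjustment is a cheap efficiency gain, not the repair of an error

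*Protocol article*

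**What the plan says.** - Section {12}, on the main endpoint: "The primary outcome measure for this study is the rate of bladder function recovery (Bladder Function Recovery Grade II or higher) 2 weeks post-surgery". This is a yes/no outcome per patient.
- Statistical methods {20a}: "Chi-square test was used for enumeration data". No covariate and no effect estimate is named; significance is declared at p < 0.05.
- Methods for additional analyses {20b}: "The primary analysis is sufficient to address the research question. No additional analyses were required". Section {20c} nevertheless plans a sensitivity analysis for missing data and a per-protocol analysis.
- Sequence generation {16a}: one computer list of 78 random numbers, split odd/even, with no stratification factor.
- Inclusion criteria: FIGO 2018 stage from IA1 to IIA1, and "Aged 20 to 65 years, and BMI < 30 kg/m^2". Stage and age must therefore be established for each patient at entry.
- Sample size {14}: "The recovery rate for the IC group was 78.95%, compared to 38.89% IDUCs group", with 35 evaluable and 39 randomised per group.

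**The concern.** Neither the randomisation nor the analysis uses patient characteristics that are already on file. The abstract attributes bladder dysfunction after this operation to a physical cause, "predominantly due to nerve damage", so extent of disease and age are plausible predictors of recovery. If they do predict it, some outcome variation that could be explained stays in the error term. With 39 per arm, a visible imbalance in such a factor would also have no planned adjusted result to set beside it. What is at stake is some precision and some credibility, chiefly if the true effect is smaller than the 40-point difference taken from the pretest.

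**Working it through.** **Inputs from the protocol.** Rates p1 = 0.7895 and p2 = 0.3889, difference 0.4006; one-sided alpha 0.025, equivalent to two-sided 0.05; power 0.90; 5% margin; 35 evaluable and 39 randomised per arm (Sample size {14}). The prognostic strength of age and stage is not given, so it is assumed and varied below.

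**1. The plan's own figure.** With z-values 1.960 and 1.282, (zα + zβ)² = 10.507. Unpooled variance with the 5% margin: (0.7895 × 0.2105 + 0.3889 × 0.6111) × 10.507 / (0.4006 − 0.05)² = 0.4039 × 10.507 / 0.1229 = 34.5, so 35 per group. With 10% dropout, 35 / 0.9 = 38.9, so 39. The printed pooled formula gives 31.7 without the margin and 41.4 with it. That is a separate matter and does not affect this point.

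**2. The chi-square as planned, 39 per arm.** Standard error of the difference: √(0.4039 / 39) = 0.102. Power at the planning rates is 0.963 (0.943 with 35 per arm). Simulated type I error is 4.9-5.3%, and the mean estimated difference is about 0.40 against a true 0.4006.

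**3. How often imbalance arises.** For a factor carried by half of the 78 patients, the hypergeometric distribution gives a 17% chance of an arm difference of 15 points or more and 7% for 20 points or more. Any 39-versus-39 trial has these figures. They say nothing about whether the factor affects the outcome.

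**4. Break-even.** With k covariates, the adjusted variance is roughly (1 − R²) × 76 / (76 − k) times the unadjusted one. Setting this to 1 gives R² = k/76: 0.026 for two covariates and 0.039 for three. Below that, adjustment costs a little; above it, it gains.

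**5. Simulation, three covariates.** Planning rates, 39 per arm, 6,000 trials per row, linear model with HC2 variance. The log-odds per SD of the combined covariate score are assumed. The variance ratio is the squared ratio of the two SDs.

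| Log-odds per SD | SD unadjusted | SD adjusted | Variance ratio | Power chi-square | Power adjusted |
|---|---|---|---|---|---|
| 0 | 0.1020 | 0.1043 | 1.05 | 0.964 | 0.955 |
| 0.3 | 0.1014 | 0.1027 | 1.03 | 0.961 | 0.956 |
| 0.6 | 0.1019 | 0.1003 | 0.97 | 0.962 | 0.965 |
| 1.0 | 0.1011 | 0.0958 | 0.90 | 0.965 | 0.978 |
| 1.5 | 0.1023 | 0.0899 | 0.77 | 0.960 | 0.989 |

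At an assumed smaller effect (65% v 38.89%), chi-square power is 0.65-0.67 and adjusted power runs from 0.64 to 0.76 over the same range.

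**6. Simulation, two covariates.** Age plus stage as one term, HC2 variance, t reference:
- Useless covariates: variance up 2-4%, power down 0.5-2 points.
- Break-even: near a log-odds of 0.3 per SD.
- Log-odds 0.6: variance down about 3-5%.
- Log-odds 1.0: variance down about 10-16%; at an assumed 69% v 39%, power rises from 78% to 83-84%.
- Type I error: 4.8-5.6% throughout.

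**7. Why the form of adjustment matters.** With stage as five categories in a logistic model followed by standardisation (assumed stage mix 8/7/35/30/20%), the variance was 1.06, 1.04 and 1.005 times the unadjusted value at log-odds 0, 0.25 and 0.5. About 20% of fits had very large coefficients, suggesting quasi-separation. Type I error was 5.5-6.6% even with a degrees-of-freedom correction. A single stage term and a small-sample variance are therefore part of the recommendation.

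**The case against.** The strongest reply is that nothing here is wrong. The test holds its level, the difference is unbiased over randomisation, and power exceeds the planned 90%. Unstratified randomisation brings no design factor that must enter the analysis. No section says that age or stage predicts 2-week recovery, and eligibility narrows their spread (early stage only, age 20 to 65). Adjustment may also be specified in an analysis plan that is not shown. All of this stands, and it makes the point a recommendation only.

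Four stronger readings might be inferred, and the documents support none of them:
- *Chance imbalance biases the result.* It is random error already reflected in the standard error.
- *Precision is certainly lost.* That needs a prognostic strength the protocol does not give; with weak covariates adjustment loses slightly.
- *Section {20b} forbids any further analysis.* It answers the item on additional analyses such as subgroups and does not mention adjustment, and {20c} plans sensitivity and per-protocol analyses.
- *The baseline data are documented as recorded.* For age and stage this follows from eligibility; the text does not list the baseline variables and Table 1 is not shown. A planned class of hysterectomy appears nowhere.

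The objection does not remove the asymmetry: the possible loss is small, the possible gain is larger, and the two covariates need no new data collection.

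**Conclusion.** The point holds as a low-cost efficiency improvement. The planned chi-square is valid and adequately powered at the planning rates, and the required sample size does not change. Adjustment for age and a single stage term ranges from a variance increase of about 2-4%, with up to about 2 points of power lost, to a variance reduction of about 3-16% at assumed log-odds of 0.6-1.0 per SD. At the planning rates there is little power left to gain. The benefit would matter mainly if the true effect is nearer 30 points than 40. These sizes rest on assumed prognostic strengths and on simulation with all 39 patients per arm analysed.

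**What to change.** In {20a}, make the primary comparison a risk difference in 2-week recovery with 95% CI, from a linear model of the 0/1 outcome on arm, age (continuous) and FIGO stage as recorded at enrolment (one ordinal or two-level term, coding fixed now). Use a small-sample robust variance such as HC2 and a t reference on 78 − 4 = 74 degrees of freedom if all are analysed. Keep the chi-square as a supportive analysis. Add no further covariates: not intraoperative variables, because allocation follows consent and not the operation, and not a hysterectomy class that the protocol does not record. Reconcile the closing sentence of {20b} with the analyses planned in {20c}.

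Cost: a short protocol amendment and a few lines of code, with no new data. Recruitment began in September 2022, so the covariates and their coding must be fixed, and the amendment dated, before anyone examines outcomes by arm. The price if age and stage prove uninformative is the small loss given in the verdict.
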